## Abstract

**Background:**

Cardiovascular risk functions fail to identify more than 50% of patients who develop cardiovascular disease. This is especially evident in the intermediate-risk patients in which clinical management becomes difficult. Our purpose is to analyze if ankle-brachial index (ABI), measures of arterial stiffness, postprandial glucose, glycosylated hemoglobin, self-measured blood pressure and presence of comorbidity are independently associated to incidence of vascular events and whether they can improve the predictive capacity of current risk equations in the intermediate-risk population.

**Methods/Design:**

This project involves 3 groups belonging to REDIAPP (RETICS RD06/0018) from 3 Spanish regions. We will recruit a multicenter cohort of 2688 patients at intermediate risk (coronary risk between 5 and 15% or vascular death risk between 3-5% over 10 years) and no history of atherosclerotic disease, selected at random. We will record socio-demographic data, information on diet, physical activity, comorbidity and intermittent claudication. We will measure ABI, pulse wave velocity and cardio ankle vascular index at rest and after a light intensity exercise. Blood pressure and anthropometric data will be also recorded. We will also quantify lipids, glucose and glycosylated hemoglobin in a fasting blood sample and postprandial capillary glucose. Eighteen months after the recruitment, patients will be followed up to determine the incidence of vascular events (later follow-ups are planned at 5 and 10 years). We will analyze whether the new proposed risk factors contribute to improve the risk functions based on classic risk factors.

**Discussion:**

Primary prevention of cardiovascular diseases is a priority in public health policy of developed and developing countries. The fundamental strategy consists in identifying people in a high risk situation in which preventive measures are effective and efficient. Improvement of these predictions in our country will have an immediate, clinical and welfare impact and a short term public health effect.

**Trial Registration:**

Clinical Trials.gov Identifier: NCT01428934

## Background

In Spain, as in most Mediterranean countries, death rates from cardiovascular diseases have traditionally been lower compared with those in Anglo-Saxon and northern and central Europe [1]. However, they are still a priority public health problem because vascular diseases contribute to 30% of total mortality in developed countries, 56 million deaths worldwide, of which more than 125, 000 are in Spain [2]. The European guideline for vascular prevention [3] recommends that prevention strategies should include three main components: 1) a population strategy to try to change lifestyle, social, environmental and economic factors which are highly related to the disease occurrence 2) a secondary prevention strategy to reduce recurrences, complications rates and improve the disease prognostic and 3) a primary prevention strategy in high-risk population in which different interventions are more efficient than in general and low-risk population. In this last strategy, the key element is to identify these individuals through the use of risk functions. This strategy has some limitations at present, since sometimes the performance of such functions is insufficient, especially in patients classified as intermediate-risk (5-15% risk at 10 years) [4]. Several attempts to improve risk functions by using new risk factors markers have not increased their predictive ability, because of the autocorrelation of these emerging factors with classical risk ones [5,6]. With the available evidence we cannot assess the balance between risks and benefits of the studied factors for its widespread use in asymptomatic men and women with no history of coronary disease [7]. The general conclusion is that this issue is a priority in vascular prevention research.

There are three opportunity areas to improve the risk estimation in intermediate-risk population:

1. The measure of subclinical atherosclerosis: Markers of atherosclerotic burden are the most reliable candidates to identify patients at increased risk of the intermediate-risk group [8]. Values below 0.9 on the ankle brachial index (ABI) are associated with an increased risk of coronary heart disease events and mortality, regardless of calculated risk by the Framingham equation [9], even in asymptomatic patients [10]. Therefore, ABI at baseline provides extra prognostic information which is not provided by the measurement of conventional risk factors alone. In our country, results have also been reported to confirm this assumption, since ABI values < 0.9 have been found to be relatively common in asymptomatic patients with coronary risk at 10 years less than 10% [11].

Arterial stiffness is also a parameter that is considered as a possible good marker of cardiovascular risk [12,13]. Traditionally, it has been quantified by pulse wave velocity (PWV). The Cardio Ankle Vascular Index (CAVI) is an index representing the stiffness of the aorta, femoral artery and tibial artery [14]. Some authors suggest that CAVI measurement, which is independent of blood pressure and has an adequate reproducibility for clinical use, is more useful as a marker of arterial stiffness than PWV [15].

2. The incorporation of more detailed and accurate assessment of traditional risk factors: The glycated hemoglobin (HbA1c) is a more accurate and stable measure than fasting glucose concentration [16]. It is more and more suggested that HbA1c concentration is not only a useful marker in patients with DM, but can also be useful to identify patients at higher risk of developing cardiovascular problems in the general population. In this regard, a recent study shows that high levels of HbA1c are associated with the occurrence of cardiovascular disease in nondiabetic patients [17] and high values of this type of hemoglobin are common in general adult population with no history of diabetes [18].

Postprandial glucose concentration has negative effects on the arterial wall and several studies have shown that a good control of postprandial glucose can revert to a reduction of cardiovascular events and mortality [19,20].

Self-measured blood pressure has a significant correlation with cardiovascular morbidity and mortality [21] and its control has some advantages such as being easily accessible and comfortable for the patient. It also has the possibility of performing multiple measurements on non-medical environment, so that white coat effect is avoided.

3. The incorporation of a comprehensive and contextualized evaluation of the patient taking into account his co-morbidity: Several studies have highlighted the importance of the presence of certain chronic diseases in vascular diseases development. There are arguments supporting that the presence of chronic obstructive pulmonary disease [22], atrial fibrillation [23], renal disease [23] and depression [24] among others are associated, independently, with an increased incidence of vascular disease. Just as the high score on composite indices of co-morbidity, has been associated with a worse prognosis of vascular diseases [25]. This suggests that this information may be useful for risk stratification, even in primary prevention.

Thus, these three lines of analysis and the proposed variables have significant scientific support as candidates to improve the population risk classification. They are also measures that can be easily and economically obtained and can be implemented in primary care, which is suitable for the population screening. The demonstration of the usefulness of some of these factors in re-stratify the population's risk will have a major impact on the primary prevention of the vascular diseases with all that this implies at the Public Health level. All this justifies the proposal to analyze their contribution to improve the predictive ability of the existing risk functions.

### Objectives

To analyze whether the ABI and arterial stiffness measures (pulse wave velocity and cardio ankle vascular index) are associated independently with the incidence of vascular events and whether they can help to improve the predictive ability of risk equations based on traditional risk factors in intermediate-risk population.

To analyze whether the postprandial capillary glucose, glycated hemoglobin, and self-blood pressure measurement are associated independently with the incidence of vascular events and whether they can help to improve the predictive ability of risk equations based on classical risk factors in intermediate-risk population.

To analyze whether the presence of comorbidity measured by composite indices (Charlson Index, Cumulative Illness Rating score) is associated independently with the incidence of vascular events and whether they can help to improve the predictive ability of risk equations based on classical risk factors in intermediate-risk population.

## Methods/Design

### Design

Multicentre prospective cohort study with a follow-up to 1.5, 5, and 10 years from the participant inclusion in the study.

### Subjects

#### Study population

Population aged between 35 to 74 years who have an intermediate cardiovascular risk, defined as coronary risk between 5% -15% at 10 years according to the Framingham adapted risk equation (because of the low incidence of coronary heart disease in our country) [26] or vascular mortality risk between 3-5% at 10 years according to the SCORE equation [27]. Exclusion criteria: terminal illness or institutionalization at the appointment time or a personal history of atherosclerotic disease. Sample selection: There will be a random sample of population aged 35 to 74 (both included) which have an intermediate cardiovascular risk. This is a multicenter project in the context of the Instituto Carlos III Preventive and Health Promotion Research Network (RedIAPP) (RETICS RD06/0018). Sample recruitment will be carried out in Health Centers belonging to 3 groups of the 3 network regions. Candidate patients will be cited by telephone at their health centre and invited to participate by signing an informed consent.

#### Sample size

The ABI < 0.9 population proportion with no history of vascular disease has been taken into account because ABI is the risk factor among those studied that we anticipate will have a lower prevalence. It is expected that in one year and a half of follow up 3% of the participants will present a vascular event. Therefore, accepting a 0.05 alpha risk and a 0.2 beta risk in a bilateral contrast, 336 subjects are needed in the exposed group and 2352 in the non-exposed group (2688 total) to detect a minimum relative risk of 2. We assumed an incidence rate in the unexposed group of 3%. Estimating a 25% of loss rate until 3360 participants will be oversampled. Poisson approximation has been used. The estimated relative risk is based on previous observational studies in which patients of the risk group had twice the incidence of vascular disease if they had an ABI < 0.9 [9]. In Catalonia node centers 1900 participants are expected to be recruited and 400 participants in each of the other two nodes. Professional nurses assigned to each health center will perform the physical examination and questionnaires. They will explain how to record the self-measurement of blood pressure and capillary blood glucose and the candidates will be cited later to collect this information. At the same time they will be scheduled for a fast blood test.

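### The protocol gives 3% as the event risk of both all participants and the unexposed, and its 80% power rests on a pooled-variance Poisson formula that is optimistic at 1:7 (about 74–76% otherwise)

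*Protocol article*

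**What the plan says.** All the inputs stand in one paragraph, Protocol article, Subjects, Sample size.

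- The calculation opens with an expectation for the whole cohort: "It is expected that in one year and a half of follow up 3% of the participants will present a vascular event".
- The next sentence draws the sample size from it: "accepting a 0.05 alpha risk and a 0.2 beta risk in a bilateral contrast, 336 subjects are needed in the exposed group", with 2352 unexposed and 2688 in total, "to detect a minimum relative risk of 2".
- It then gives the event risk as an input for one group: "We assumed an incidence rate in the unexposed group of 3"%.
- The method is named in one sentence: "Poisson approximation has been used". Which variance enters the formula is not said.
- The exposure is ABI < 0.9. The section says its prevalence was taken into account but prints no value. The group sizes imply 336/2688 = 12.5%.

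**The concern.** The same 3% is attached to two different populations. If exposure doubles the risk, the overall risk must exceed the unexposed risk, so one of the two sentences is wrong. The choice between them changes the power.

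The method sentence also leaves room for a shortcut. With seven unexposed subjects for each exposed one, the variance of the risk difference is much larger under the alternative than under the null. A formula that uses the null variance throughout will then overstate power.

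At stake is the claim that 2688 participants give 80% power at 1.5 years for ABI < 0.9, the exposure on which the cohort is sized.

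**Working it through.** **Inputs (all from Sample size).** Two-sided alpha 0.05 (z = 1.960); beta 0.2 (z = 0.842); RR 2; n1 = 336 exposed and n0 = 2352 unexposed, so 1:7; 3% either in the unexposed or overall; Poisson approximation. (1.960 + 0.842)² = 7.849.

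**1. Compatibility of the two 3% statements.** Overall risk = p0 × (0.875 + 0.125 × 2) = 1.125 × p0.
- p0 = 3% gives 3.375% overall and 6% in the exposed.
- 3% overall gives p0 = 0.03/1.125 = 2.67% and p1 = 5.33%.

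**2. Reproducing the plan's figure (3% unexposed).** Pooled rate = (0.06 + 7 × 0.03)/8 = 0.03375. With this rate as Poisson variance in both terms:

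n1 = 7.849 × 0.03375 × (8/7) / 0.03² = 336.4, so 336 and 7 × 336 = 2352.

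Power at 336/2352: the standard error is √[0.03375 × (1/336 + 1/2352)] = 0.010714, and 0.03/0.010714 − 1.960 = 0.840, which gives 79.96%. The stated figure reproduces.

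**3. Same formula, 3% overall.** Pooled rate 0.03, difference 0.02667.
- n1 = 7.849 × 0.03 × (8/7) / 0.02667² = 378.4, or about 3027 in total (× 8).
- Power at 336/2352: 0.02667/0.010102 − 1.960 = 0.680, which gives 75.2%.

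**4. The pooled-variance shortcut.** Per exposed subject, the Poisson variance with 3% unexposed is 0.03375 × 8/7 = 0.0386 under the null and 0.06 + 0.03/7 = 0.0643 under RR 2, which is 67% larger. With each variance in its own place:

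power = Φ[(p1 − p0 − 1.960 × SE0)/SE1]

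- Poisson, 3% unexposed: SE0 = 0.010714, SE1 = √(0.06/336 + 0.03/2352) = 0.013832; (0.03 − 0.0210)/0.013832 = 0.651, which gives 74.2%. For 80%, n1 = 398, about 3182 in total.
- Two proportions, 3% unexposed: SE0 = 0.010532, SE1 = 0.013425; the argument is 0.697, which gives 75.7%. For 80%, n1 = 381, total 3048.
- 3% overall: 70.1% (Poisson) and 71.4% (two proportions).

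**5. Simulation at 336/2352, two-sided 0.05.**

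| Data and test | 3% unexposed | 3% overall |
|---|---|---|
| Poisson data, score test | 74.1% | 69.8% |
| Binomial data, uncorrected chi-square | 75.6% | 71.1% |

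**6. Does 336 identify which 3% was used?** Not quite on its own. If the unexposed rate alone serves as the variance in both terms, 3% overall also gives 7.849 × 0.02667 × (8/7)/0.02667² = 336.4. That formula is cruder, since it gives the exposed group no larger variance, and it does not match the sentence that names the unexposed group. The pooled calculation in step 2 is the natural reading, but the sponsor should confirm it.

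**The case against.** The strongest reply is that nothing fails to compute. The section names a Poisson approximation and a 3% risk in the unexposed, and with these 336/2352 follows almost to the digit. The sentence about all participants can be read as a looser statement of expectation. Other formulas also sit near 80% at these group sizes: 80.5% for a binomial log relative risk and 81.3% for pooled binomial variance. The 2688 is the number meant to remain after losses, since the section adds an oversample. Follow-up at 5 and 10 years will bring more events.

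Much of this stands.

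- A reader might infer that 80% does not follow from the plan's own inputs, or that the sum is wrong. The protocol does not support that, because the figure reproduces.
- A reader might also take 71% as the plan's power if 3% is overall. On the plan's own formula it is 75%; 71% needs the change of formula as well.
- Lower prevalences of ABI < 0.9, such as 8% or 10%, would reduce power further, but the protocol gives no basis for them.
- The power figures above cannot be described as before loss to follow-up.

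The reply does not remove the contradiction. The sentence on all participants leads directly into the calculation, so it cannot be set aside as background. Nor does reproducing 80% show that the design has it. The tests simulated with 3% unexposed fall short, including a score test on data generated as Poisson (74.1%) and a Wald test of the log relative risk (75.3%), whose analytic approximation looked more favourable.

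**Conclusion.** The concern holds in two parts. First, 3% cannot be the 1.5-year risk of both all participants and the unexposed at RR 2 with 12.5% exposed. If it is the overall risk, power on the plan's own formula is about 75% rather than 80%. Second, 80% depends on carrying the pooled null variance into the beta term. With the variance proper to each hypothesis the design has about 74–76% power (3% unexposed) or about 70–71% (3% overall).

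These figures assume exactly 336 exposed and 2352 unexposed with outcome known, and an unadjusted two-group comparison at 1.5 years. The pooled-variance form of the Poisson approximation is inferred from the match to 336, since the article does not print its formula. The weight is moderate: the shortfall is roughly 4 to 10 percentage points in a planning figure, and it does not invalidate the cohort or its later follow-ups.

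**What to change.** In the Sample size section:

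- Say which risk the 3% is. Keeping it as the unexposed risk fits the explicit input sentence and the pooled formula that gives 336. The sentence on all participants should then read about 3.4%. If 3% was meant as the overall risk, recompute with 2.67% and 5.33%.
- State the assumed prevalence of ABI < 0.9, which the group sizes put at 12.5%. Label any other prevalence as a sensitivity assumption.
- Name the variance used, and restate the power at 2688 as about 74–76% (about 70–71% if 3% is overall), noting that 80% comes from the pooled-variance Poisson formula.

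The cost is a few sentences and a less favourable power figure. No participants need be added. If the sponsor prefers to hold 80% with 3% unexposed, the totals are 3048 (two proportions) to about 3182 (Poisson).

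### The 25% loss allowance multiplies 2688 by 1.25 (3360) instead of dividing by 0.75 (3584), so the stated target covers only a 20% loss

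*Protocol article*

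**What the plan says.** All the sizing is in the Sample size section of the protocol article. The error rates are set by "accepting a 0.05 alpha risk and a 0.2 beta risk in a bilateral contrast". The unexposed group is assumed to have a 3% incidence of vascular events over the first 1.5 years. From these inputs the section concludes that "336 subjects are needed in the exposed group and 2352 in the non-exposed group (2688 total) to detect a minimum relative risk of 2", and it names the method: "Poisson approximation has been used".

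The loss allowance is one sentence: "Estimating a 25% of loss rate until 3360 participants will be oversampled". No other loss-adjusted figure appears in the article.

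Two further counts bear on the target. The Sample size section expects 1900 participants from the Catalonia centres and 400 from each of the other two nodes. The Abstract (Methods/Design) gives the cohort to be recruited as 2688.

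**The concern.** The need (2688), the loss rate (25%) and the inflated number (3360) cannot all hold. A loss rate is a share of the people who start, so the starting number is the need divided by the share retained. Adding 25% of the need instead gives a number that is too small.

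The consequence is that if 3360 start and the loss is as planned, the study still misses its own requirement. The section sizes the study on ABI < 0.9 because it expects that factor to be the rarest of those studied, so the shortfall also reduces an exposed group that is already small.

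**Working it through.** **Inputs** (all from the Sample size section): two-sided alpha 0.05; power 0.80; relative risk 2; 3% incidence in the unexposed, hence 6% in the exposed; 336 exposed and 2352 unexposed, a ratio of 1:7; Poisson approximation; loss 25%; inflated number 3360.

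**Step 1. Reproduce the plan's base number.** The section does not print its formula. A Poisson normal approximation with the pooled rate as the variance under both hypotheses gives

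- pooled rate = (0.06 + 7 × 0.03) / 8 = 0.03375
- n exposed = (1.960 + 0.842)² × 0.03375 × (1 + 1/7) / (0.06 − 0.03)² = 336.4

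This matches 336, and 7 × 336 = 2352, total 2688. Other common formulas do not give 336: two proportions 381 (419 with continuity correction), Poisson with pooled variance under the null and unpooled under the alternative 398, log relative risk 350. The pooled-rate Poisson form is therefore taken as the plan's own.

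**Step 2. Reproduce the inflated number.** 2688 × 1.25 = 3360 exactly. The allowance was applied as N × (1 + d).

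**Step 3. Apply the stated loss.**

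- 3360 × 0.75 = 2520, that is 315 exposed and 2205 unexposed
- shortfall = 2688 − 2520 = 168, and 168 / 2688 = 6.25%
- loss that 3360 does cover = 1 − 2688 / 3360 = 20%
- number needed for 2688 after a 25% loss = 2688 / 0.75 = 3584 (448 exposed, 3136 unexposed), 224 more than 3360

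**Step 4. Effect on power for a relative risk of 2.** On the plan's formula, z = √[n × 0.03² / (0.03375 × 8/7)] − 1.960.

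| Evaluable | Exposed | Plan's Poisson formula | Two-proportion formula |
|---|---|---|---|
| 2688 | 336 | √7.84 − 1.960 = 0.840, power 80% | 75.7% |
| 2520 | 315 | √7.35 − 1.960 = 0.751, power 77.4% | 73.4% |

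The loss step costs about 2.6 points on the plan's formula and 2.3 points on the other. Expected events fall from 336 × 0.06 + 2352 × 0.03 = 90.7 to 315 × 0.06 + 2205 × 0.03 = 85.1.

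**Step 5. Compare with the other counts.** 1900 + 400 + 400 = 2700. This is close to 2688 but matches neither 3360 nor 3584. If 2700 were the number enrolled and 25% were lost, 2700 × 0.75 = 2025 would remain (about 253 exposed), and the plan's formula gives √5.906 − 1.960 = 0.470, or about 68% power.

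**The case against.** Five points can be made on the other side.

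1. *The 25% may be an oversampling margin, or 3360 may be a number sampled or invited and not a number enrolled.* The sentence is awkward enough to allow either reading, and the section on limitations does name participation as a major difficulty. But the sentence calls the 25% a loss rate, and 25% off 3360 is 2520 whichever group the 3360 counts. This stands only as uncertainty about what 3360 counts.

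2. *The effect is small.* This stands. The relative risk detectable with 80% power on the plan's formula moves only from 2.00 to about 2.04. The 25% is itself a round planning figure, and if the loss is 20% or less, 3360 is enough. No objective, endpoint or analysis method is affected.

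3. *The power could be said to fall from 80% to 73%.* A reader might infer this by setting the two-proportion result at 2520 against the plan's 80%. The document does not support it. The two-proportion formula already gives only 75.7% at the full 2688, and the plan states that it used a Poisson approximation. Most of that apparent gap comes from changing the formula.

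4. *Replacing 3360 by 3584 would settle the matter.* It would not. The node expectations and the Abstract would still disagree with the target, and going from 2700 to 3584 actual recruits means 884 more people. The 68% in Step 5 depends on reading 2700 as the number before losses, which the section does not say in so many words. It belongs to the reconciliation and is not a consequence of the inflation step.

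5. *Follow-up continues to 5 and 10 years, when more events accrue.* True, but the sample-size statement is made for 1.5 years. This limits the consequence without repairing the figure.

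**Conclusion.** The arithmetic error is certain, because the inputs and the result stand in the same paragraph and the result does not follow. At the stated 25% loss, 3360 leaves 2520 evaluable, 168 (6.25%) below the plan's own requirement; it covers a 20% loss. The cost is about 2.6 points of power on the plan's method (80% to 77.4%). This rests on the stated 3% and 6% risks, a 1:7 ratio kept after losses, and the pooled-rate Poisson formula inferred from its match to 336.

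This is a minor to moderate correction. It does not show that the study is seriously underpowered. The open question with more practical weight is which of 2688, 2700 and 3360 is the number to be recruited.

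**What to change.** Amend the loss sentence in the Sample size section in one of two ways:

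- keep 3360, and state that 2520 evaluable participants are expected after a 25% loss, with about 77% power for a relative risk of 2 on the plan's Poisson formula; or
- state that 3360 allows for a 20% loss, if that rate can be supported.

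In either case, note that 3584 would be needed to retain 2688 at a 25% loss.

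In the same edit, say whether 3360 counts people sampled, invited or enrolled, and reconcile it with the 2700 recruits expected from the three nodes and the cohort of 2688 in the Abstract, stating for each whether it is before or after losses.

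The wording change costs a few lines and, under the first option, a slightly lower stated power. Raising enrolment to 3584 is a different matter: 224 people above the stated 3360, or 884 above the 2700 that the nodes expect.

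### The node recruitment figures sum to 2700, which matches the sample size before the loss allowance (2688) and not the inflated 3360; with the stated 25% loss, 18-month power for ABI would be about 68%, not 80%.

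*Protocol article*

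**What the plan says.** All the figures are in the protocol article.

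- **Requirement.** Under Sample size: "336 subjects are needed in the exposed group and 2352 in the non-exposed group (2688 total) to detect a minimum relative risk of 2", with the error rates given as "accepting a 0.05 alpha risk and a 0.2 beta risk in a bilateral contrast". The assumed 18-month incidence in the unexposed group is 3%.
- **Loss allowance.** Same paragraph: "Estimating a 25% of loss rate until 3360 participants will be oversampled".
- **Recruitment by node.** Same paragraph: "In Catalonia node centers 1900 participants are expected to be recruited and 400 participants in each of the other two nodes". The Study population section confirms that recruitment takes place in three groups from three regions, so there is no fourth source.
- **Abstract, Methods/Design.** "We will recruit a multicenter cohort of 2688 patients at intermediate risk".

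**The concern.** Three numbers describe the size of the cohort, and they do not fit together. The number needed with outcome data is 2688. The number after allowing for loss is 3360. The only operational figures, those for the nodes, add up to roughly the first. The loss allowance is thus stated but assigned to no node, and the abstract presents the pre-loss number as the number to be recruited.

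At stake is the power claim for the 18-month analysis of ABI below 0.9. The sample was sized on ABI because the authors expect it to be the least prevalent of the factors studied, and ABI belongs to the first objective. A null ABI result at 18 months could be read as coming from a study with 80% power when its power was clearly lower.

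**Working it through.** **Inputs (Sample size section).** Two-sided alpha 0.05; power 0.80; 336 exposed and 2352 unexposed, a ratio of 1:7 (12.5% exposed); incidence 3% in the unexposed, hence 6% in the exposed at relative risk 2; loss rate 25%; inflated number 3360; node figures 1900, 400 and 400.

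**1. Reproduce the stated requirement.** The text names only a Poisson approximation, so the formula has to be inferred. Take the difference of two rates, with the pooled Poisson variance used under both hypotheses:

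- pooled rate = (0.06 + 7 × 0.03) / 8 = 0.03375
- n exposed = (1.960 + 0.842)² × 0.03375 × (8/7) / 0.03² = 7.849 × 0.038571 / 0.0009 = 336.4

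This agrees with 336 exposed and 2688 in total. A log relative risk formula with binomial variance comes close as well (332 exposed, 2656 in total), so the attribution is an assumption.

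**2. Reproduce the inflation.** 2688 × 1.25 = 3360. Because 3360 × 0.80 = 2688, this figure covers an actual loss of 20%. Both 20% and 25% loss are therefore carried through below.

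**3. Add the node figures.** 1900 + 400 + 400 = 2700. That is 660 below 3360 (660/3360 = 20%) and 12 above 2688 (12/2700 = 0.4%).

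**4. Apply the loss to 2700.**

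- 25% loss: 2700 × 0.75 = 2025, of whom about 253 exposed and 1772 unexposed. Expected events: 2025 × 0.03375 = 68, against 2688 × 0.03375 = 91.
- 20% loss: 2700 × 0.80 = 2160, of whom 270 exposed. Expected events: 73.

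**5. Power for relative risk 2, same formula throughout.** Power = Φ(0.03/SE − 1.960), with SE = √(0.038571 / n exposed). The detectable relative risk solves the same equation for 80% power, with the pooled rate recomputed for each value.

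| Evaluable | n exposed | SE | 0.03/SE | Power | Relative risk detectable with 80% power |
|---|---|---|---|---|---|
| 2688 | 336 | 0.01071 | 2.800 | 80.0% | 2.00 |
| 2160 | 270 | 0.01195 | 2.510 | 70.9% | 2.12 |
| 2025 | 253.1 | 0.01234 | 2.430 | 68.1% | 2.16 |

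**6. Sensitivity to the formula.** The binomial log relative risk formula gives 81% at 2688 and 69% at 2025, about the same fall. The standard two-proportion formula gives 66% at 2025 but only 76% at 2688. Its 66% must be set against its own 76%, not against the stated 80%.

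**The case against.** **The 3360 may be people approached.** The text speaks of oversampling to 3360 but of recruiting 2700. Candidates are randomly sampled and invited by telephone, and the limitations section names participation as a major difficulty. On this reading 2700 enrolled agrees with both 2688 and the abstract. The reading is possible but weaker: the sentence refers to a loss rate and to participants, and participation is discussed separately. It also leaves a cohort followed by telephone at 1.5, 5 and 10 years with a margin of 12 people. What stands is that the loss of power is conditional on 2700 enrolling and on the loss occurring after enrolment.

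**The node figures are expectations.** A reader might infer that the nodes will stop at these numbers, so that 80% power is certain to be missed. The document does not support that. It states no quota, cap or stopping rule, and nodes could exceed their forecasts. The fair statement is narrower: no recruitment figure in the article carries the loss allowance.

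**A larger fall in power is tempting.** A reader might set 66% power, or a detectable relative risk of about 2.26, against the stated 80% and 2.00. Both come from the two-proportion formula, which gives 76% power and a detectable relative risk of 2.07 at the full 2688. Part of that contrast is a change of formula and not a recruitment gap.

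**The consequence is limited.** This is an observational cohort, the calculation concerns one factor at the first of three follow-ups, and the 5- and 10-year contacts will accrue more events. The Cox models can also use time contributed by people lost after a contact. This bounds the harm to the 18-month ABI analysis but does not remove the inconsistency.

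**Conclusion.** The point holds as an internal inconsistency with a measurable consequence. The node figures (2700) and the abstract (2688) match the requirement before loss, while the same section says 3360 are needed to cover loss.

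If 2700 enrol, 18-month power for ABI at relative risk 2 is about 68% with the stated 25% loss and about 71% with 20% loss. The detectable relative risk is about 2.16 and 2.12 respectively. These figures rest on four assumptions: 3% incidence in the unexposed, 12.5% exposed, loss unrelated to exposure or outcome, and the inferred pooled Poisson formula. The article states all the conflicting numbers itself, so a fuller protocol or analysis plan would not make them agree.

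**What to change.** Reconcile 2688, 2700 and 3360 in the Sample size section by one of two routes.

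- **Keep 2700.** Restate the plan as about 2025 evaluable at 18 months with 25% loss, giving about 68% power for relative risk 2, or 80% for a relative risk of about 2.16. Name the formula used.
- **If 3360 is the true target,** correct the node figures so that they sum to it.

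On either route, state whether 3360 counts people approached or people enrolled, and have the abstract distinguish participants recruited from participants with follow-up.

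The first route changes only text and costs nothing beyond a less favourable power figure. The second means finding 660 more participants than the nodes now expect (3360 − 2700).
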